### Study design

The study includes 104 health sub-districts from 48 districts in Eastern and Western Uganda. The unit of randomisation is one health sub-district (cluster). Clusters were randomly assigned to receive one of four types of LLINs, including two LLINs with PBO: 1) PermaNet 3.0 (*n* = 32) and 2) Olyset Plus (*n* = 20); and two LLINs without PBO: 3) PermaNet 2.0 (*n* = 37) and 4) Olyset Net (*n* = 15). Prior to distribution of the nets, baseline surveys of community households and children aged 2–10 years, and entomological surveillance for insecticide resistance monitoring, were conducted (Fig. 1). LLINs were distributed within the study area by the Ministry of Health between March 2017 and March 2018. The evaluation includes follow-up community and entomology surveys at 6, 12, and 18 months post-distribution, plus assessment of net durability and bio-efficacy at 12 months. The primary outcome of the trial is parasite prevalence, measured by microscopy in children aged 2–10 years in the follow-up community surveys.

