### Sample size calculations

#### Community surveys

The study sample size (number of clusters and allocation of interventions) was set by the number of nets available for the four different types of study nets and the estimated number of LLINs required per cluster. We will sample all eligible children aged 2–10 years from 50 households in the 104 clusters in each round of surveys, resulting in an estimated total of 10,400 children from 5200 households per survey. Assuming a parasite prevalence of 40% in the control arm [25], and coefficient of variation between clusters of 0.3 (derived from the ongoing trial in Tanzania [21]), we will have 80% power (two-sided significance level of 0.05) to detect a relative reduction in parasite prevalence of at least 17% (prevalence ratio of 0.83).

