#### Statistical methods

All data will be analysed on the basis of intention-to-treat and per-protocol analyses. Intention-to-treat analyses will include the assigned treatment arms and results from all clusters. For per-protocol analyses, clusters will be grouped by treatment arm according to the type of LLINs actually received in the national campaign. For clusters with mixed LLIN distribution, the number of nets from the dominant type received (numerator) will be divided by the total number of the four study net types received in that cluster, excluding non-study nets (denominator). To be included in the per-protocol analyses, the proportion of the dominant net received in the cluster must be > 75% out of the four study net types. Clusters in which the dominant net type received is ≤ 75% will be excluded from the per-protocol analyses. The primary outcome will be the prevalence of asexual parasitaemia from the cross-sectional surveys. An individual-level approach to the analysis will be used due to the large number of clusters per arm. For comparison of the primary outcome between treatment arms, generalized linear Poisson models with a log-link function will be used to allow for within-cluster correlations adjusting for baseline cluster-level parasite prevalence. The effect of the intervention will be quantified by calculation of a prevalence ratio. Separate analyses will be performed using data from the post-distribution cross-sectional surveys (performed 6, 12, and 18 months after the delivery of the nets).

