## Trial status

The baseline community and entomology surveys were carried out from March to June 2017. LLINs were distributed in the study area between March 2017 and March 2018. The first round of follow-up surveys (6 months) started in September 2017 and the final round of surveys (18 months) are scheduled to complete in September 2019. We are seeking funding for an additional round of surveys, which would be conducted at 24–30 months following distribution of the LLINs.

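### One primary hypothesis is analysed separately at 6, 12 and 18 months, and nothing says which result, or which combination of results, decides it

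*Protocol article*

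**What the plan says.** **Hypothesis and outcome.** Under Primary objective and hypothesis there is one comparison, PBO against conventional nets, with no time point. Study design gives the outcome: "The primary outcome of the trial is parasite prevalence, measured by microscopy in children aged 2–10 years in the follow-up community surveys". The abstract also refers to the follow-up surveys in the plural.

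**Analysis.** Statistical methods describes a Poisson model with log link, adjusted for baseline cluster prevalence and giving a prevalence ratio. It closes with "Separate analyses will be performed using data from the post-distribution cross-sectional surveys" and lists 6, 12 and 18 months. No survey is singled out. There is no combined test, no requirement on how many surveys must agree, and no adjustment for testing more than once. Monitoring rules out an interim analysis, so this is not a group-sequential scheme.

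**Sample size.** Under Sample size calculations, Community surveys, the calculation rests on one round, "resulting in an estimated total of 10,400 children from 5200 households per survey". It states "we will have 80% power" at a "two-sided significance level of 0.05" to detect a prevalence ratio of 0.83. This is the only significance level in the document.

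**The concern.** One question receives three answers, and the plan does not say how they become one conclusion. If PBO nets look better at 6 months but not at 12 or 18, a reader cannot tell from the plan whether the primary hypothesis was supported. Disagreement is a real possibility, because the Background expects impact to depend on how well PBO is retained.

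The 0.05 in the power statement is the error rate of one test on one survey. It is the error rate of the primary claim only if a single test decides that claim. The trial is meant to inform net policy in Uganda and across Africa, so the error rate behind its main conclusion should be known.

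**Working it through.** **Inputs from the article.** Control prevalence p0 = 0.40 and prevalence ratio 0.83, so p1 = 0.40 × 0.83 = 0.332. Between-cluster coefficient of variation k = 0.3. There are 52 clusters per arm. Children per cluster per survey: m = 10,400 / 104 = 100. Two-sided 0.05.

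**Assumed input.** The correlation ρ between the three survey-specific tests is not given. I use 0 to 0.86. The upper end follows from the plan's own inputs if cluster effects persist fully between surveys and there is no baseline adjustment:
- between-cluster variance: k²p0² = 0.09 × 0.16 = 0.0144
- sampling variance: p0(1 − p0)/m = 0.24/100 = 0.0024
- ρ = 0.0144 / (0.0144 + 0.0024) = 0.86

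**Step 1: reproduce the stated power.** The Hayes–Bennett formula for unmatched clusters is

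c = 1 + (1.96 + 0.84)² × V / (p0 − p1)², with V = p0(1 − p0)/m + p1(1 − p1)/m + k²(p0² + p1²).

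- V = 0.00462 + 0.02432 = 0.02894
- clusters needed per arm: 50.1, against 52 available
- standard error with 52 per arm: √(0.02894/51) = 0.02382
- z = 0.068/0.02382 = 2.855, so power = Φ(2.855 − 1.960) = 81.5%
- ratio detectable at 80% power: 0.833

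The stated figure therefore reproduces as one full 0.05 test on one survey round. A design-effect version (intracluster correlation 0.06) gives 78.1%, also close to 80%.

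**Step 2: error rate if each survey is tested at two-sided 0.05.** For independent tests, the chance of at least one false positive is 1 − 0.95³ = 14.3% in either direction and 1 − 0.975³ = 7.3% in favour of PBO. For equally correlated normal test statistics, the same probabilities come from a one-dimensional integral.

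| ρ | Either direction (nominal 5%) | Favouring PBO (nominal 2.5%) |
|---|---|---|
| 0 | 14.3% | 7.3% |
| 0.5 | 12.5% | 6.3% |
| 0.7 | 10.9% | 5.5% |
| 0.86 | 9.1% | 4.5% |

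**Step 3: power of one pooled test at ratio 0.83.** Under a common effect, averaging three surveys multiplies the variance by (1 + 2ρ)/3. Power is then Φ(2.855/√[(1 + 2ρ)/3] − 1.960).

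| Test | Variance factor | Power | Detectable ratio at 80% power |
|---|---|---|---|
| One survey | 1 | 81.5% | 0.833 |
| Pooled, ρ = 0.86 | 0.905 | 85.1% | 0.841 |
| Pooled, ρ = 0.7 | 0.800 | 89.1% | 0.849 |
| Pooled, ρ = 0.5 | 0.667 | 93.8% | 0.862 |

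For comparison, keeping three tests with a Bonferroni split (0.05/3 = 0.0167 each) gives 67.8% power per survey and a detectable ratio of 0.809.

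**The case against.** **No significance level is attached to the separate analyses.** This stands. A reader might infer that the plan tests each survey at 5% and counts a win at any one as success. The text states neither; 0.05 per survey is carried over from the power statement. The inflation is conditional on that reading. The missing rule is not.

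**The hypothesis is directional, so the two-sided figures overstate false PBO successes.** This also stands. The relevant range is about 4.5–7.3% against 2.5%: still inflated, but about half the either-direction figures.

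**A full protocol or analysis plan may settle it.** This stands in part. Details of multiplicity are often left to such documents, and the closing sentence does not expressly exclude an overall comparison. But the article does not leave the analysis open. It specifies separate analyses for an outcome it defines across surveys, and the choice of deciding comparison belongs with the definition of the primary outcome.

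**Separate analysis is not an error of power.** Correct. One survey is adequately powered on the stated inputs. At correlation 0.86 pooling adds only about four points. A lower correlation after baseline adjustment would also improve the single-survey test, which the comparison above leaves unadjusted. It is tempting to say the plan throws away substantial power, but its own inputs do not establish that.

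**A further survey might look like a fourth chance.** Trial status says only: "We are seeking funding for an additional round of surveys, which would be conducted at 24–30 months following distribution of the LLINs". Nothing places that round in the primary analysis, and Statistical methods lists three surveys, so it is not counted here.

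**If PBO wanes, survey-specific effects are a legitimate target.** Agreed. This is a reason to report them and to choose the deciding test deliberately; it does not justify leaving the choice open.

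**Conclusion.** The concern holds in this form: the article fixes three separate analyses for one primary hypothesis, sizes the trial for one of them, and gives no rule that turns three results into one conclusion. The error rate of the primary claim is therefore undefined.

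The 9–14% and 4.5–7.3% ranges assume a full two-sided 0.05 test at each survey, a claim of success on any one of them, and a correlation between 0 and 0.86. Because the same 104 clusters are resurveyed, 14.3% is the upper end and should not be taken as the expected value. The pooled-power figures also assume an effect common to all three surveys.

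**What to change.** By a dated amendment, made before any arm-level comparison of follow-up data, name one primary test at two-sided 0.05. The preferred choice is a single model on the 6-, 12- and 18-month data together, with survey as a factor, one PBO effect, adjustment for baseline cluster prevalence, and clustering at health sub-district. Report survey-specific prevalence ratios from an arm-by-survey interaction as secondary. Naming one survey as primary would also resolve the problem.

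No extra data or clusters are needed, but it is more than a wording change. Follow-up began in September 2017 and was due to finish in September 2019, so the amendment needs ethics approval and a registry update, as the article requires, and should state whether anyone had seen follow-up results by arm.

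The statistical downside is that the headline becomes an average over 18 months and could mask waning. The secondary survey-specific ratios would show it, but no single survey could then be declared positive on its own.

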#### Sub-group analyses

Stratified sub-group analyses will be performed at the level of the region (Western or Eastern) and net manufacturer (PermaNet or Olyset). Spatial auto-correlation in insecticide resistance will also be explored to interpolate resistance patterns collected at the household level.

### Monitoring

Given the nature of this trial, in which the intervention (LLINs) is delivered as a national programme by the Uganda Ministry of Health, no data and safety monitoring committee was established, and we have no plans for an interim analysis. Moreover, as the investigators are responsible only for the evaluation, we have no plans for monitoring adverse events. Internal audits of the trial are being conducted for each round of surveys by the IDRC’s regulatory department.

## Ethical issues

### Research ethics approval

The trial has been approved by the Ugandan National Council for Science and Technology (UNCST; ref. HS 2176), Makerere University School of Medicine Research & Ethics Committee (SOMREC; 2016–133), London School of Hygiene and Tropical Medicine Ethics Committee (LSHTM; ref. 12019), and the Liverpool School of Tropical Medicine (LSTM; ref. 16–072), which sponsored the study.

### Protocol amendments

Approval of the original study protocol (V2.0, 1 February 2017) was obtained from all of our Institutional Review Boards (IRBs) on 13 March 2017. The protocol was subsequently amended (Version 3.0, 15 August 2017), and was fully approved on 1 November 2017. For any future protocol amendments, investigators will be notified, IRB approval will be sought, and the clinical trial registry will be updated. For the SPIRIT 2013 Checklist of recommended items to include in an interventional trial protocol, see Additional file 2.

### Informed consent

Approval from local leaders will be sought before beginning activities in the project area. Written informed consent to participate in the study will be obtained by the head of household (or their designate) for all households participating in the community and entomology surveys. Written consent to participate in the clinical survey will be obtained from parents or guardians of all children. In all cases involving participation of children aged 8 years or older, written assent will also be obtained from the child. All informed consent discussions will be conducted in the appropriate local language, and a translator will be used if necessary. Information sheets and consent forms will be available in English and appropriate local languages, describing the purpose of the project and the procedures to be followed, and the risks and benefits of participation. During the consent discussions, each section of the consent form will be read exactly as it is written either by study personnel or by the translator, and then further explained to the respondent (participant or parent/guardian) if necessary. The translator will also assist with the discussion and assessment of comprehension. All participants and parents/guardians will be informed that participation in the study is completely voluntary and that they may withdraw from the study at any time. If the person asked to provide consent is unable to read or write, their fingerprint will substitute for a signature, and a signature from a witness to the informed consent procedures will be obtained. Written consent for future use of biological specimens will also be obtained for the community surveys.

### Confidentiality

Records for this study will be maintained and stored in compliance with the principles of GCP and regulatory and institutional requirements, and in compliance with the requirements for the protection of confidentiality of participants. Only study personnel will have access to these records. All forms with participant names will be kept in a locked cabinet when not in use. Participants will be identified by their study ID number, and participant names will not be included in databases used for analysis. Data will be stored for at least 10 years. Anonymized data collected in this study may also be shared with other investigators and/or placed into the public domain via a data repository.

### Ancillary and post-trial care

Given the nature of this trial, in which the intervention (LLINs) is delivered as a national programme by the Uganda Ministry of Health and the evaluation includes assessments of community members at a single point in time, there are no plans to provide ancillary or post-trial care.

### Dissemination policy

The final 18-month cross-sectional survey will be conducted in September 2019. Laboratory testing, data analyses, and preparation of the final manuscript are expected to take until the end of 2019. Peer-review and publication of the trial results are anticipated in the first quarter of 2020. We plan to disseminate the findings widely, sharing with the sponsor and key stakeholders, including the Uganda Ministry of Health and the National Malaria Control Division, the World Health Organization’s Vector Control Advisory Group, Innovative Vector Control Consortium, President’s Malaria Initiative, and Global Fund, among others. The results will also be presented at national and international conferences. Authorship for the Long-Lasting Insecticidal Net Evaluation in Uganda Project (LLINEUP) manuscripts was decided in advance by the core investigators; no professional writers will be used. Access to the full protocol, participant-level dataset, and statistical code will be available upon reasonable request.

## Trial status

The baseline community and entomology surveys were carried out from March to June 2017. LLINs were distributed in the study area between March 2017 and March 2018. The first round of follow-up surveys (6 months) started in September 2017 and the final round of surveys (18 months) are scheduled to complete in September 2019. We are seeking funding for an additional round of surveys, which would be conducted at 24–30 months following distribution of the LLINs.

## Discussion

The WHO has issued a preliminary endorsement of PBO LLINs based on the results of a single trial conducted in Tanzania, but additional evidence of the effect of PBO LLINs is urgently needed. Uganda, with its persistently high burden of malaria and widespread pyrethroid resistance, is an optimal setting to undertake this evaluation. We have leveraged resources by applying a cluster-randomised design to a national LLIN distribution campaign aiming to achieve universal coverage of LLINs in Uganda. Although this study design, linking the evaluation to the national LLIN campaign, presents substantial opportunities, it also presents a few limitations. Because the nets were procured in advance of establishing the trial, the type and number of nets were already fixed. Thus, we were required to use adaptive randomisation to accommodate for the differences in net availability. The shortage of nets available for the final round of distribution in the study area forced the Ministry of Health to source additional nets; as a result, the research team had to re-randomise the final 60 clusters. Moreover, the Ministry of Health and partners, not the research team, were responsible for distributing the nets. Although we worked closely with the Ministry of Health to ensure that the LLINs were allocated according to the randomisation list, there is a chance that the net distribution was imperfect. Despite these challenges, this innovative trial design demonstrates how policy makers, programme implementers, and researchers can work together to generate robust scientific evidence on the impact of malaria control interventions delivered at a national level.

### Trial sponsor

This trial is sponsored by the Liverpool School of Tropical Medicine (LSTM); Research Protocol (#16–072).

## Abbreviations

GCP: Good Clinical Practice
IDRC: Infectious Diseases Research Collaboration
IRS: Indoor residual spraying
LLIN: Long-lasting insecticidal net
LLINEUP: Long-Lasting Insecticidal Net Evaluation in Uganda Project
LSHTM: London School of Hygiene and Tropical Medicine
LSTM: Liverpool School of Tropical Medicine
PBO: Piperonyl butoxide
RDT: Rapid diagnostic test
SOP: Standard operating procedure
UBOS: Uganda Bureau of Statistics
WHO: World Health Organization
